# OnTrack Chile for people with early psychosis: a study protocol for a Hybrid Type 1 trial

**DOI:** 10.1186/s13063-022-06661-7

**Published:** 2022-09-05

**Keywords:** Early psychosis, Hybrid Type 1 trial, Global mental health, Specialized coordinated services for first episode psychosis, Coordinated specialty care

## Abstract

**Background:**

Substantial data from high-income countries support early interventions in the form of evidence-based Coordinated Specialty Care (CSC) for people experiencing First Episode Psychosis (FEP) to ameliorate symptoms and minimize disability. Chile is unique among Latin American countries in providing universal access to FEP services through a national FEP policy that mandates the identification of FEP individuals in primary care and guarantees delivery of community-based FEP treatments within a public health care system. Nonetheless, previous research has documented that FEP services currently provided at mental health clinics do not provide evidence-based approaches. This proposal aims to address this shortfall by first adapting OnTrackNY (OTNY), a CSC program currently being implemented across the USA, into OnTrackChile (OTCH), and then examine its effectiveness and implementation in Chile.

**Methods:**

The Dynamic Adaptation Process will be used first to inform the adaptation and implementation of OTCH to the Chilean context. Then, a Hybrid Type 1 trial design will test its effectiveness and cost and evaluate its implementation using a cluster-randomized controlled trial (RCT) (*N* = 300 from 21 outpatient clinics). The OTCH program will be offered in half of these outpatient clinics to individuals ages 15-35. Usual care services will continue to be offered at the other clinics. Given the current COVID-19 pandemic, most research and intervention procedures will be conducted remotely. The study will engage participants over the course of 2 years, with assessments administered at enrollment, 12 months, and 24 months. Primary outcomes include implementation (fidelity, acceptability, and uptake) and service outcomes (person-centeredness, adherence, and retention). Secondary outcomes comprise participant-level outcomes such as symptoms, functioning, and recovery orientation. Over the course of the study, interviews and focus groups with stakeholders will be conducted to better understand the implementation of OTCH.

**Discussion:**

Findings from this study will help determine the feasibility, effectiveness, and cost for delivering CSC services in Chile. Lessons learned about facilitators and barriers related to the implementation of the model could help inform the approach needed for these services to be further expanded throughout Latin America.

**Trial registration:**

www.ClinicalTrials.govNCT04247711. Registered 30 January 2020.

**Trial status:**

The OTCH trial is currently recruiting participants. Recruitment started on March 1, 2021, and is expected to be completed by December 1, 2022. This is the first version of this protocol (5/12/2021).

## Background

Absent early intervention, schizophrenia spectrum disorders often become long-term disabling conditions with profound impacts on individuals, their families, and society at large [1]. Loss of income and costs of services compound these impacts. Substantial data support early interventions for people experiencing first episode psychosis (FEP) to ameliorate symptoms and minimize disability in the early phase of psychosis [2], and trials of FEP programs have been widely and successfully conducted in high-income countries (HICs) [3–5]. In Latin America, Chile is the only country that offers universal access to FEP services.

Chile has been one of the leaders of mental health reform in Latin America, serving as a model for the region [6]. Most of its population receive health and mental health care via the public system into which we plan to introduce evidence-based FEP services. Almost everyone living in the poorest or “marginal” communities in urban areas in Chile utilizes the public system. In terms of FEP, Chile has implemented two fundamental reforms that facilitate implementing and scaling up an evidence-based program. First, as of 2005, government legislation mandates that any person with FEP has the right to community-based treatment in the public health system free of charge or with an affordable co-payment [7] and requires that any person who is under evaluation for FEP be recorded in a “national FEP register.” This register records useful information, including the number of people with FEP identified annually in every locale of Chile [7]. Second, psychiatric hospital beds have been progressively replaced by an extensive network of outpatient mental health services in the public health care system [6] and psychiatric units within general hospitals. Mental health services are offered within a primary care system that covers the entire country. The primary care clinics are affiliated with specific mental health outpatient clinics to which they refer individuals they have identified as needing mental health services. This creates a single point of entry into mental health services for the population, including people with FEP. This centralized system offers an opportune environment for examining the implementation and scale-up of evidence-based FEP services in Chile. Furthermore, it will inform how to build structures for FEP services in other Latin American countries, many of which are already moving in this direction even those with less resources.

Nonetheless, previous studies have documented two crucial gaps in FEP services in Chile. First, primary care providers are not adequately trained to identify and refer individuals with FEP to outpatient clinics [8]. Second, the mental health services being provided for people with FEP are not up to date and not totally supported by current evidence [9]. For example, although over 80% of people treated for FEP in Chile receive medications, only 40% receive other important services such as support for education and employment, family counseling, and peer support [8, 9]. Moreover, when these other services are offered, they tend to be ad-hoc because most mental health providers are not appropriately trained in evidence-based approaches (i.e., psychosocial interventions) for psychosis [9, 10]. This is the gap that is being addressed by the current study by first adapting OnTrackChile (OTCH) from OnTrackNY (OTNY), a coordinated specialty care (CSC) program for FEP currently being implemented across the US, and then examining its effectiveness and implementation across five different regions in Chile. OTNY is appropriate for adaptation to OTCH because it is (1) an evidence-based program with high rates of engagement among users associated with improvements in symptoms and functional outcomes [2, 11]; (2) scaled up to serve individuals throughout New York state by working closely with state and local mental health authorities [12]; and (3) practical and scalable with good fidelity [13].

Accordingly, the overarching goal of this Hybrid Type 1 trial is to evaluate the effectiveness and implementation of OTCH in 21 mental health clinics. We will use the Dynamic Adaptation Process model [14] to inform the adaptation and implementation of OTCH in the Chilean context, and then use a cluster-RCT (*N* = 300) to test the model’s effectiveness and cost. The primary outcomes in the cluster-RCT will be implementation outcomes (fidelity, acceptability, and uptake) at the provider- and participant-level, and service outcomes (patient-centeredness, adherence, and retention) at the participant-level. We will also examine moderators of implementation at the community-, provider-, and participant-level. Secondary outcomes will be clinical effectiveness including symptoms, functioning, and recovery orientation at the participant-level. We will also test whether implementation and service outcomes are mediators of clinical effectiveness and estimate the total and incremental costs of the intervention. Finally, we will use a set of qualitative measures to learn about the experiences with FEP services among clients, family members, providers, and policy makers.

## Research objectives

Aim 1: Evaluate the implementation of OTCH at 12 months and 24 months in a cluster-RCT.Compare OTCH vs Usual FEP care on service and implementation outcomes.Examine whether factors at community-, provider-, and participant-level moderate service and implementation outcomes of OTCH vs Usual FEP care.

Aim 2: Evaluate the effectiveness of OTCH vs Usual FEP Care at 12 months and 24 months.Compare the effectiveness of OTCH vs Usual FEP care on symptoms, functioning, and recovery orientation.Test both Service and Implementation Outcomes at 12 months as mediators of the effectiveness of OTCH vs. Usual FEP care at 24 months.

Aim 3: Estimate the cost of delivering OTCH vs Usual FEP care over a 24-month period.

## Methods/design

### Study design

This effectiveness-implementation Hybrid Type 1 trial aims to examine both the implementation and effectiveness of OTCH. A Hybrid Type 1 design, as we propose, tests the effects of a clinical intervention on client-level outcomes, while at the same time exploring multi-level implementation factors that can inform and promote the use of the intervention in real-world settings. It has been proposed as a solution to accelerate the process of transferring evidence-based practices into usual care. Moreover, the Dynamic Adaptation Process (DAP) [14] will be used to adapt and implement OTCH, as well as to examine fidelity and document implementation barriers and facilitators. The DAP provides a way to thoroughly identify and incorporate adaptations at multiple levels and facilitate implementation across the whole study. In contrast to most dissemination and implementation models, within the DAP, modifications, and adaptations are made by a team exclusively devoted to this task known as “Research Adaptation Team,” who is composed of multiple stakeholders and aimed to reflect what was learned about: a) understanding contextual conditions, and how context might be modified; and b) how these conditions might modify the nature of the content of the intervention curriculum.

A cluster-RCT will be conducted among 300 participants with FEP drawn from 21 outpatient clinics that include marginalized and poor communities to test the effectiveness of OTCH (see Fig. 1 below based on PRISMA guidelines).

**Fig. 1 Fig1:**
[figure not shown]
Flow diagram of the cluster RCT

### Description of sites

Twenty-one outpatient clinics located in five different regions in Chile will be enlisted in this study. The regions involved in the study include the Metropolitan Region of Santiago with a population of 7,112,808; the IV region of Coquimbo with a population of 757,586; the V region of Valparaíso with a population of 1,815,902; the VI region of O’Higgins with a population of 914,555; and the VII region of Maule with a population of 1,044,950. In these regions, more than 80% of the total population uses the public health system. Thirteen of the 21 clinics are in the Santiago Metropolitan region, which is divided in 4 health districts: Southern, Western, Southeastern, and Central Metropolitan. Further information regarding population served, poverty level, and expected enrollment for each of the twenty-one clinics is available upon request.

### Adaptation process

As noted previously, we will use the Dynamic Adaptation Process (DAP) to adapt and implement OTCH, examine fidelity, and document barriers and facilitators. The implementation of OTCH will include four phases: Preparation, Adaptation, Implementation, and Evaluation (Fig. 2). Ongoing experience will iteratively inform adaptation as needed. We will convene multiple stakeholders (e.g., policy makers, providers, clients) in qualitative interviews and focus groups to discuss contextual conditions and identify potential modifications to the OTCH model and training curriculum. Then, once OTCH teams are established, a centralized training team will provide ongoing training using a virtual learning platform which will facilitate synchronous and asynchronous learning opportunities including virtual meetings, treatment manuals, tools, videos and other resources to support implementation. We will use mixed methods to examine to examine the implementation of OTHC to identify facilitators and barriers throughout the trial and to capture adaptation through the trials. In line with the Dynamic Adaptation Process, the qualitative data collected during the preparation phase will be presented and discussed with the OTCH clinical team as they are establishing their implementation to determine areas for adaptation via consensus. As the teams are implementing the OTCH model, the research team will use the DAP to allow us to systematically evaluate modifications made and ascertain their impact. Our approach captures processes for modification including reasons for the modification, what was modified, level of modification, and timing across phases of treatment. We also continue to examine the implementation and adaptations carried forth through OTCH teams during the 6 and 18-month qualitative data collection activities.

**Fig. 2 Fig2:**
[figure not shown]
Dynamic Adaptation Process

### Sample size and power analysis

The first phase of the study which focused on the qualitative data collection did not include any formal power calculation to determine the sample size. Instead, we took a multistakeholder approach to include participants at different levels involved in the care for people with FEP including users and their family members. To incorporate a variety of stakeholder perspectives, we aimed to conduct 10 focus groups with 6–8 stakeholders.

For the cluster trial, power was calculated conservatively based on the participation of 270 participants (rather than the full 300 to be enrolled), anticipating a possible participant drop-out of ~10%. We estimated that, with at least 10 clinics in each condition, we will have 80% power to detect a difference in mean outcomes between study conditions with a moderate effect size of Cohen’s *d* = 0.35 following the standard detectible effect size formula for clustered randomized trials [15, 16]. This power calculation was derived assuming an intra-class correlation of 0.05 for outcomes by clinic (15 participants nested within 21 clinics). We also assume an alpha of 0.05 and that all tests are 2-tailed. Previous research has shown interventions like OTCH to have moderate to large effects on implementation and service outcomes, such as medication adherence, service utilization, and engagement in treatment [5, 17]. We have also shown that FEP providers in Chile rely primarily upon medication and are usually not trained to promote shared decision-making, recovery orientation, or person-centered care [9]. Then it is reasonable to anticipate at least moderate (and probably large) effects of OTCH on these indicators of implementation. Finally, evidence for the expected effect on participant-level symptoms and functioning comes from the RAISE Connection Program study, which indicated improvement over 24 months for participants enrolled (e.g., PANSS improvement effect size 0.91, occupational functioning 1.2, and social functioning 0.72) [17]. Power to detect mediation effects (Aim 2b) depends on the size of the effect of intervention on implementation and service outcomes (path a), and the correlation between implementation and services outcomes and participant level symptoms, functioning, and recovery (path b). Based on tabulated recommendations for sample sizes needed to test mediation effects with a sample of size *N*=270 with follow-up data, we have over 80% power to detect a significant mediation effect with path a=.26 and b=.26. Path a is expected to be >0.35 (argued for Aim 1 above), and we expect based on our previous work that there will be at least moderate associations between implementation and clinical outcomes (*r*>0.40), assuming no confounding of mediator-outcome relationship.

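### The stated 80% power at d = 0.35 does not follow from the plan's own inputs, which give about 58–62% power and a detectable effect of about 0.43–0.45

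*Protocol article*

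**What the plan says.** All the inputs are in the protocol article, under Sample size and power analysis.

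- Analysed sample: "power was calculated conservatively based on the participation of 270 participants", that is, 300 enrolled less about 10% drop-out.
- Clinics: at least 10 per condition; 21 take part.
- Clustering: "assuming an intra-class correlation of 0.05 for outcomes by clinic (15 participants nested within 21 clinics".
- Error rate: "We also assume an alpha of 0.05 and that all tests are 2-tailed".
- Method: the standard detectable-effect formula for cluster randomised trials.
- Result: "we will have 80% power to detect a difference in mean outcomes between study conditions with a moderate effect size", which is put at d = 0.35.

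The calculation mentions no gain from baseline covariates, repeated measures or matching. For the clinical outcomes, the section cites effect sizes of 0.91, 1.2 and 0.72 from an earlier early-psychosis programme, "which indicated improvement over 24 months for participants enrolled".

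**The concern.** The section publishes the inputs, the method and the result together, so the result can be checked. An ICC of 0.05 with about 13 participants per clinic inflates the variance by more than half. It is therefore surprising that 270 participants should still detect 0.35, close to the limit for 270 independent participants.

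At stake is what the trial can be said to have been built to find. At 80% power a true effect of 0.35 is missed 2 times in 10; at 58–62% it is missed about 4 times in 10. A reader who relies on the stated figure would give a non-significant result more weight against an effect of that size than it deserves. The section also describes its calculation as conservative.

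Two smaller matters sit beside this. The cluster size does not agree with either total. The only effect sizes cited for symptoms and functioning are described as improvement among enrolled participants, which is a change over time and not a difference between arms.

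**Working it through.** **Inputs** (all from Sample size and power analysis): N = 270; 21 clinics, taken as 10 v 11; ICC 0.05; two-sided alpha 0.05; d = 0.35 with SD 1. Equal clinic sizes are assumed.

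**Formulas.** Design effect DE = 1 + (m − 1) × ICC. SE = √[DE × (1/n₁ + 1/n₂)]. Power = Φ(d/SE − 1.960), or noncentral t with df = clinics − 2. Detectable d at 80% power = (1.960 + 0.842) × SE, or the t equivalent.

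**Plan's figure at its own inputs**

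- m = 270/21 = 12.86
- DE = 1 + 11.86 × 0.05 = 1.593; effective N = 270/1.593 = 169.5
- n₁ = 128.6, n₂ = 141.4; SE = √[1.593 × (1/128.6 + 1/141.4)] = 0.154
- d/SE = 0.35/0.1538 = 2.276; power = Φ(2.276 − 1.960) = 62%; with t on 19 df, 58%
- Detectable d = 2.802 × 0.1538 = 0.431; with t, 0.454

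The stated 80% is not reproduced.

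**Other two-sided readings of the stated inputs, ICC 0.05**

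| Reading | DE | Power at 0.35 (z / t) | Detectable d (z / t) |
|---|---|---|---|
| 270 in 21 clinics | 1.593 | 62.4% / 57.9% | 0.431 / 0.454 |
| 270 in 20 clinics | 1.625 | 61.6% / 56.9% | 0.435 / 0.460 |
| 270, with m = 15 in the DE | 1.700 | 59.6% / 55.2% | 0.445 / 0.469 |
| 300 in 21 clinics, no loss | 1.664 | 65.1% / 60.5% | 0.418 / 0.440 |
| 300 as 20 × 15, no loss | 1.700 | 64.2% / 59.5% | 0.422 / 0.446 |
| 315 as 21 × 15, no loss | 1.700 | 66.3% / 61.7% | 0.412 / 0.434 |

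The highest figure is 66%. Even a one-sided alpha of 0.05, which contradicts the text, gives at most 77%.

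**What would give 80%?**

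- ICC = 0 with N = 270: power 82%, detectable d = 2.802 × √(4/270) = 0.341.
- Solving for the ICC that gives 80% (normal): about 0.0045 at N = 270 and about 0.016 at N = 315, against 0.05 stated.

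**Cluster size.** 15 × 21 = 315. The totals imply 300/21 = 14.3 enrolled, or 270/21 = 12.9 analysed, per clinic.

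**Unequal clinics.** The Randomization section matches clinics on expected enrolment, so sizes will differ. With a coefficient of variation of 0.5 (an assumption; the article gives none), DE = 1 + [(1 + 0.25) × 12.86 − 1] × 0.05 = 1.754, and the detectable d is 0.45 (z) or 0.48 (t).

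**The case against.** The best defence is that a gain in precision was used and not written down. Most outcomes are measured at baseline, and the Aim 2a model includes the baseline time point. If baseline and follow-up correlate at about 0.6 at both clinic and participant level (assumed), 270 participants give about 81% power (z) or 77% (t). If a correlation of 0.7 acts only within clinics, the figure is 77% (z). Averaging the 12- and 24-month values, with within-person correlations of 0.3 to 0.7 (assumed), gives 67–73%.

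This shows that 80% is not out of reach for some analysis, but it does not rescue the statement. The section describes a plain difference in means and states no correlation. The Aim 1a analysis only considers adding covariates if baseline differences appear. No gain from matching is claimed either.

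A second objection is that the protocol expects at least moderate, and probably large, effects on the implementation indicators. At d = 0.5 the same inputs give about 87–90% power. That stands, and it limits the practical harm. It does not make the figure for 0.35 correct.

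A third is that 15 per clinic is probably 14.3 rounded up. That is plausible, and the inconsistency is minor; it slightly raises the design effect.

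A reader might also infer that the mediation power falls with the corrected figure. The text does not support this. Mediation power is taken from tabulated sample sizes at N = 270 with both paths at 0.26, not from the clustered detectable effect. The link to Aim 1 concerns only the expected size of path a.

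**Conclusion.** The point holds. On the inputs as printed, power at d = 0.35 is about 62% (normal) or 58% (t, 19 df), a shortfall of 18 to 22 percentage points. The effect detectable with 80% power is about 0.43 to 0.45. No two-sided reading of the stated inputs exceeds 66%. These figures assume equal clinic sizes and no covariate adjustment; unequal sizes would lower power, and a strong baseline covariate would raise it.

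Three stronger readings are not supported:

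- That the design effect was left out. The match at ICC = 0 (82%, d = 0.341) suggests this, but the article does not say so, and the sources cited for the formula are not at hand.
- That 58–62% describes all six primary outcomes. Acceptability is rated by providers, and fidelity draws on provider feedback, supervision calls and site visits. A calculation on 270 participants does not describe those.
- That the trial must enrol more. The finding is that a published statement is wrong on its own inputs.

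The effect sizes of 0.91, 1.2 and 0.72 are a lesser matter. They concern secondary clinical outcomes and do not enter the 0.35 calculation. As worded, however, they are change over time and do not support a between-arm effect.

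**What to change.** Replace the power statement with wording such as: *For participant-level outcomes, with 270 participants in 21 clinics (mean 12.9 per clinic, equal sizes assumed), ICC 0.05 and two-sided alpha 0.05, without covariate adjustment, the trial has 80% power for d of about 0.43 (normal) to 0.45 (t, 19 df) and about 58–62% power for d = 0.35; unequal clinic sizes would lower this.* If a variance reduction was in fact used, state instead what it was and the value assumed.

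Change the figure of 15 per clinic so that it agrees with the N used. Either drop the three 24-month improvements as support for the expected effect or label them as change over time.

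The cost is wording only. The stated detectable effect becomes less favourable; enrolment, design and analysis are unchanged.

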Based on prior research [43–45], we have hypothesized that service and implementation outcomes at 12 months will mediate the impact of OTCH on clinical outcomes at 24 months. To establish service and implementation outcomes at participant- and provider-level at 12 months as mediators of the OCTH effect on user-level clinical symptoms, functioning, and recovery orientation at 24 months, in addition to finding intervention effects (OCTH vs FEP usual care) as in Aim 1a and Aim 2a, we must also establish that service and implementation outcomes at 12 months are associated with better participant symptoms, functioning, and recovery orientation at 24 months. The mediation effect [46] is estimated by taking the expected value of the total effect of OTCH vs FEP Usual Care on symptoms, functioning, and recovery, and subtracting the direct effect when service and implementation outcomes are considered. This indirect (or mediation) effect of the implementation factors will be estimated and tested by fitting a Structural Equation Model using MPlus version 7.4 which our lead statistician has extensive expertise. We will estimate mediation models that consider one implementation or service mediator at a time, as well as including all indicators of implementation or service simultaneously to identify independent effects. The bootstrapping method (available in Mplus) will be used to obtain standard errors, confidence intervals, and the test for statistical significance [47]. Even in an RCT, the association between the mediator and the outcome can be confounded by other time-varying confounders and recent developments in mediation analysis suggest the need for sensitivity analyses to explore the potential impact of unmeasured confounders. We will perform these sensitivity analyses which provide a range of plausible results that may have been obtained under different assumptions about unmeasured confounders [48].

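### The mediation power statement sets a Cohen's d of 0.35 against a path requirement of .26 as if both were on one scale, and makes no allowance for clinics

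*Protocol article*

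**What the plan says.** All the power statements are in the protocol article under 'Sample size and power analysis'. For Aim 1, with an ICC of 0.05 and 21 clinics, the trial is said to have 80% power for a "difference in mean outcomes between study conditions with a moderate effect size of Cohen’s *d* = 0.35". The number used is 270 of 300: "power was calculated conservatively based on the participation of 270 participants". On error rates: "We also assume an alpha of 0.05 and that all tests are 2-tailed".

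For Aim 2b the basis changes: "Based on tabulated recommendations for sample sizes needed to test mediation effects". With N = 270, "we have over 80% power to detect a significant mediation effect with path a=.26 and b=.26". The next sentence gives the reason to think this is met: "Path a is expected to be >0.35 (argued for Aim 1 above"). Path b is expected to exceed r = 0.40. The scale of .26 is not stated, and no clinic adjustment is mentioned for mediation.

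Under 'Aim 2a and 2b analyses' the mediation effect is estimated with a structural equation model. "The bootstrapping method (available in Mplus) will be used to obtain standard errors, confidence intervals, and the test for statistical significance". Clinics and the resampling unit are not mentioned there. Under 'Aim 1a and Aim 1b analyses', by contrast, the model has clinic-level random effects.

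**The concern.** A power statement for mediation has two parts: the path sizes that give the stated power, and a reason to expect paths at least that large. Here the first part is .26 and the reason is 0.35. They can be compared only if they are on the same scale. Sample-size tables for mediation are usually indexed by standardized paths, whereas 0.35 is a difference in standard deviation units between two arms. With two near-equal arms, a standardized path is about half the corresponding d.

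In addition, path a is the effect of a treatment allocated by clinic. Its precision depends on the ICC that the same section assumes, but the mediation figure uses 270 as if participants were independent.

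At stake is how Aim 2b is read. If power is thought to exceed 80% and is really nearer 60% at the only effect size the article gives, a non-significant indirect effect will be taken too readily as evidence against the proposed mechanism.

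**Working it through.** **Inputs.** From 'Sample size and power analysis': N = 270; two-sided alpha 0.05; 21 clinics; ICC 0.05; a = b = .26 for the power figure; d = 0.35 anticipated for path a; r = 0.40 anticipated for path b. Average clinic size is 270/21 = 12.86.

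**Method.** Mediation is declared when both paths are significant, so power is about power(a) × power(b). For a standardized path, z = path × √N. For a Cohen's d between equal arms, z = (d/2) × √N. √270 = 16.43.

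**Step 1: the plan's figure, standardized scale, no clustering.** z = .26 × 16.43 = 4.27, so each path has power 0.990. Jointly, 0.990 × 0.990 = 0.98. Simulation with a percentile bootstrap (2,000 trials, 500 resamples) gave 98.1%. The stated figure is reproduced, with room to spare.

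**Step 2: the same figure with clinics.** Design effect = 1 + (12.86 − 1) × 0.05 = 1.593; effective N = 270/1.593 = 169.5; √169.5 = 13.02. Path a: z = .26 × 13.02 = 3.39.
- Normal approximation: 0.923 × 0.990 = 0.91.
- t with 19 df (21 clinics less 2): 0.894 × 0.990 = 0.88.
- Design effect on both paths: 0.923 × 0.923 = 0.85.
- Reading .26 strictly as a correlation (d = 0.54): z = 0.27 × 13.02 = 3.51, power 0.94, joint 0.93.

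So the figure for a = b = .26 stays above 80% at the protocol's own ICC.

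**Step 3: put 0.35 on that scale.** r = d/√(d² + 4) = 0.35/√(0.1225 + 4) = 0.17. Conversely, d = 2 × .26/√(1 − .26²) = 0.54. The anticipated 0.35 therefore falls short of the .26 it is meant to exceed.

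**Step 4: the other reading, .26 as a d.** z = 0.13 × 16.43 = 2.14, power(a) = 0.57, joint 0.56, without clustering. Now 0.35 does exceed .26, but the stated power fails.

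**Step 5: mediation power at d = 0.35.**

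| Case | Path a: z | Joint power, b = .26 | Joint power, b = .40 |
|---|---|---|---|
| No clustering | 0.175 × 16.43 = 2.88 | 81% | 82% |
| ICC 0.05, normal | 0.175 × 13.02 = 2.28 | 62% | 62% |
| ICC 0.05, t 19 df | 2.28 | 57% | 58% |

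Path b is not the bottleneck. The scale slip takes power from 98% to 81%, and the clinics take it from 81% to about 60%. With b = .26, other ICCs give 77% (normal) and 72% (t) at 0.01, and 49% and 45% at 0.10. In simulation at ICC 0.05, a clinic-level joint test gave 57%, and a whole-clinic bootstrap 65 to 67%. Solving for 80% at ICC 0.05 gives d = 0.44 (normal) or 0.46 (t).

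The power of path a is simply the Aim 1 power. The article's 80% at d = 0.35 is reproduced only without clustering (82%); with the design effect above it is 62% (normal) or 58% (t).

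**Step 6: the analysis, if participants were resampled.** With no true path a and ICC 0.05, an analysis that ignores clinics rejects path a with probability 2 × Φ(−1.96/√1.593) = 0.12. Simulated participant-level bootstraps gave 12.7% (b = .26) and 13.2% (b = .40). A whole-clinic bootstrap gave 8.4 to 8.8%, and a clinic-level joint test about 5%.

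**The case against.** Four replies deserve weight.

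First, a reader might infer that the over-80% sentence is itself false. It is not. On the standardized scale, the only one on which it can be reproduced, it is correct and survives an ICC of 0.05. What fails is the next sentence, which supplies the reason for expecting a path that large. This reply stands, and it limits the point.

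Second, 0.35 is offered as a floor. The article anticipates effects that are at least moderate and probably large, and at d of about 0.46 or more the power is there. That is fair, but 0.35 is the only figure given for path a, and it is the one used to show that the requirement is met.

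Third, a reader might infer that the planned bootstrap will inflate false mediation findings. The document does not support that. It does not name the resampling unit, and an article may leave this to the full plan. It also requires, before mediation is claimed, intervention effects as in Aim 1a, and that model has clinic random effects. With no true path a, that condition holds back false claims. The 12 to 13% therefore applies only to a participant-level bootstrap used alone.

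Fourth, the table behind the calculation is not available, so the scale of .26 is inferred. This does not rescue the argument, because both possible scales were checked.

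**Conclusion.** The point holds as an inconsistency within the power section. The justification (0.35, a Cohen's d) and the requirement (.26) cannot both be right on one scale, and no allowance for clinics is stated for the mediation power. At the plan's own d = 0.35 and ICC 0.05, power for mediation is about 57 to 62% by a joint test of both paths, against the implied 80% or more. The shortfall below 80% comes from the scale slip and the clinics together; either alone would leave power above 80%.

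The handling of clinics in the mediation model is a conditional risk to be clarified and not a shown error.

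These figures assume the same ICC of 0.05 for the mediator, near-equal clinic sizes, a participant-level mediator, unit residual variance and no direct effect. They do not cover mediators measured on providers or clinics. They also leave out the further condition that an effect on the clinical outcome be found, which could only lower the chance of a mediation claim.

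**What to change.** State the scale of path a and replace the mediation power sentences with something like: *At d = 0.35 on the mediator (standardized path about 0.17), ICC 0.05, 21 clinics, N = 270 and b of at least .26, power for mediation is about 57 to 62% by a joint test of both paths; 80% needs d of about 0.44 to 0.46.* If a larger effect is expected, give it as a number with its basis.

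Secondarily, say that path a in the mediation model will be tested with clinic-level inference, in line with the Aim 1 model: for example a two-level model, or a joint test with clinic-level degrees of freedom. A simple whole-clinic bootstrap should not be the only remedy, since with 21 clinics it still left about 8 to 9% false positives in simulation.

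The cost is wording and analysis code. Sample size and conduct do not change. The stated power becomes less favourable, and the intervals will be wider than under an analysis that ignores clinics.
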